## Abstract

**Background:**

Accurate detection of patients with minimal residual disease (MRD) after surgery for stage II colon cancer (CC) remains an urgent unmet clinical need to improve selection of patients who might benefit form adjuvant chemotherapy (ACT). Presence of circulating tumor DNA (ctDNA) is indicative for MRD and has high predictive value for recurrent disease. The MEDOCC-CrEATE trial investigates how many stage II CC patients with detectable ctDNA after surgery will accept ACT and whether ACT reduces the risk of recurrence in these patients.

**Methods/design:**

MEDOCC-CrEATE follows the ‘trial within cohorts’ (TwiCs) design. Patients with colorectal cancer (CRC) are included in the Prospective Dutch ColoRectal Cancer cohort (PLCRC) and give informed consent for collection of clinical data, tissue and blood samples, and consent for future randomization. MEDOCC-CrEATE is a subcohort within PLCRC consisting of 1320 stage II CC patients without indication for ACT according to current guidelines, who are randomized 1:1 into an experimental and a control arm.

In the experimental arm, post-surgery blood samples and tissue are analyzed for tissue-informed detection of plasma ctDNA, using the PGDx elio™ platform. Patients with detectable ctDNA will be offered ACT consisting of 8 cycles of capecitabine plus oxaliplatin while patients without detectable ctDNA and patients in the control group will standard follow-up according to guideline.

The primary endpoint is the proportion of patients receiving ACT when ctDNA is detectable after resection. The main secondary outcome is 2-year recurrence rate (RR), but also includes 5-year RR, disease free survival, overall survival, time to recurrence, quality of life and cost-effectiveness. Data will be analyzed by intention to treat.

**Discussion:**

The MEDOCC-CrEATE trial will provide insight into the willingness of stage II CC patients to be treated with ACT guided by ctDNA biomarker testing and whether ACT will prevent recurrences in a high-risk population. Use of the TwiCs design provides the opportunity to randomize patients before ctDNA measurement, avoiding ethical dilemmas of ctDNA status disclosure in the control group.

**Trial registration:**

Netherlands Trial Register: NL6281/NTR6455. Registered 18 May 2017, https://www.trialregister.nl/trial/6281

## Background

In patients with stage II colon cancer (CC) the recurrence rate (RR) after surgery is approximately 15–20% [1]. Disease management after surgical resection in stage II CC is still under debate, because the overall survival (OS) benefit of adjuvant chemotherapy (ACT) in this group of patients varies between 2 and 5% only [2, 3]. Moreover, offering ACT in a low-risk population induces an important amount of overtreatment with unnecessary, but sometimes severe toxicity, and costs.

Several prognostic characteristics of stage II CC have been identified to provide better selection of patients that might benefit from ACT. Patients with presence of at least one of the following characteristics are classified as being at high risk of disease recurrence: poorly differentiated histology, pT4 lesions, inadequately (less than 12) sampled lymph nodes, lymphovascular or perineural invasion or tumor presentation with perforation or obstruction [4].

In contrast, patients with a deficient mismatch repair (dMMR) status in stage II CC have a low risk of recurrence and ACT is not considered beneficial, irrespective of the presence of other risk factors [5, 6]. Other known prognostic factors in CC, like gene expression profiles or BRAF (V600E) and RAS mutations, have been investigated but do not adequately identify the patients that will benefit from ACT [7–9].

Despite the definition of high- and low risk subgroups of stage II CC patients, retrospective analyses demonstrated that improved survival after administration of ACT was not observed in high risk patients, or exclusively in patients with a pT4 tumor [10–12]. Therefore in the Netherlands, ACT is currently only recommended in stage II CC patients with a pT4 tumor without dMMR.

Unfortunately, also pT4 is not an absolute predictor for disease recurrence in stage II patients. In a retrospective analysis of 995 stage II CC patients with pT4 tumors, the 3-year disease-specific survival rate after surgery was 91% in patients who received ACT and 73% in patients who did not receive ACT, which means that 73% of these patients are exposed to ACT unnecessarily [12]. Considering non-pT4 stage II patients, a population registry analysis of 40,338 patients showed that in this group 12.5% of patients suffered from recurrences [13]. These data demonstrate that using pT4 as a prognostic factor results in significant under- and overtreatment.

Minimal residual disease (MRD) is defined as the presence of tumor cells in the blood, bone marrow or lymph nodes not detected by conventional staging procedures [14]. Patients who have MRD after surgery are not completely cured and therefore at high risk of developing disease recurrence. Development of a highly specific and sensitive (bio)marker test indicative for MRD would allow identification of the subset of patients likely to experience recurrence of disease, thereby improving the selection of patients who may benefit from adjuvant treatment. In adjuvant trials, this would solve problems of high numbers needed for inclusion and dilution of effectiveness of adjuvant treatment by inclusion of many already cured participants [15].

Cell-free circulating tumor DNA (ctDNA) has a strong potential for being this sensitive, and yet specific biomarker. ctDNA consists of small fragments (usually 150–200 bp) of tumor-derived DNA containing tumor-specific mutations which can be detected in liquid biopsies such as blood samples [16–18]. Because of the short half-life of ctDNA (estimates ranging from 15 to 120 min) the presence of ctDNA in blood samples taken several days after surgery presumably reflects a state of MRD [19–21]. Patients with MRD have the highest risk for disease recurrence.

Recently, the presence of ctDNA after tumor resection demonstrated a very strong prognostic value for disease recurrence in stage II CC, with a 2-years RR of 79.0% versus 9.8% in patients with and without detectable ctDNA after surgery respectively [21]. In this study the univariate prognostic value of ctDNA was much higher than that of pT4 status (hazard ratio of 14 versus 2.6, respectively). There are several ongoing trials that use ctDNA in prognostication (NCT03637686, NCT03737539, NCT03416478, NCT03312374, NCT02842203, NCT03615170) and treatment (NCT03748680, ACTRN12615000381583, NRG-GI 005) of non-metastatic CC, but to date there are no results available of randomized controlled trials (RCTs) that use ctDNA for selection of ACT treatment.

The accumulating evidence for the strong prognostic value of ctDNA raises an important ethical dilemma for randomization of patients when designing a conventional RCT, in which patients with detectable ctDNA are randomized into ACT treatment or standard of care follow-up while disclosing ctDNA status to the control group. Indeed, the knowledge of having a very high chance of disease recurrence will be a big burden for patients with detectable ctDNA in the control group and their caregivers as they are not being offered any additional therapy. This warrants an innovative trial design different from the conventional RCT, like the ‘Trial within Cohorts’ (TwiCs) design [22–25]. The TwiCs design enables an experimental group in which ctDNA status is disclosed and a control group that is unaware of their ctDNA status.

The MEDOCC-CrEATE trial is designed as a multicenter TwiCs study with two parallel groups in which we will investigate whether stage II CC patients with detectable ctDNA after resection are willing to receive ACT and whether ACT reduces the RR in these ctDNA-positive patients.

## Methods/design

### Aim

This study investigates the willingness of patients to receive ACT after detection of ctDNA post-surgery and the effect of ctDNA-guided ACT on the RR in stage II CC patients.

### Study design

The MEDOCC-CrEATE trial follows the TwiCs design and is performed within the Prospective Dutch ColoRectal Cancer cohort (PLCRC; www.PLCRC.nl) [26]. PLCRC is set up by the Dutch Colorectal Cancer Group (DCCG) and collects clinical data and Patient Reported Outcome Measures (PROMs) at baseline and at multiple time points during follow-up (Fig. 1). At enrollment, patients give informed consent for use of their clinical data and optionally for receiving quality of life questionnaires, collection of biomaterials for research, additional sequential blood sampling and for being approached for future studies conducted within the infrastructure of the cohort, either in accordance with the TwiCs design or not.

**Fig. 1 Fig1:**
[figure not shown]
Schematic presentation of MEDOCC-CrEATE, using the trial within cohort (TwiCs) design. **a** PLCRC is a nationwide cohort study in the Netherlands with inclusion of CRC patients (all stages). By optional informed consent regarding collection of biomaterials and future randomization, observational as well as interventional trials can be performed within the cohort. **b** Non-metastatic CRC patients are included in MEDOCC when the patient signs informed consent for PLCRC including additional blood sampling. Blood samples are withdrawn before resection, 4–21 days after resection and every 6 months during the first 3 years of follow-up. **c** Eligible stage II colon cancer patients are randomized 1:1 following the TwiCs design. In the experimental group informed consent is being asked for immediate ctDNA analysis of the blood sample obtained after resection. If ctDNA is detectable, patients are offered adjuvant chemotherapy. The control group is not informed about MEDOCC-CrEATE and will receive standard of care

### Patient selection and recruitment

Patients will be recruited in both academic and non-academic hospitals in the Netherlands that are participating in PLCRC. Non-metastatic colorectal cancer (CRC) patients that give informed consent for PLCRC including consent for additional blood sampling at enrollment, will be included in the observational PLCRC substudy MEDOCC (Molecular Early Detection of Colon Cancer) before surgery. The participants are eligible for the current MEDOCC-CrEATE trial if they meet the following criteria after surgery: (1) histopathological confirmed and radically resected stage II CC; (2) age ≥ 18 years; (3) informed consent for PLCRC and MEDOCC including consent for randomization in future trials and use of tissue; (4) physical condition allows treatment with combination chemotherapy consisting of a fluoropyrimidine and oxaliplatin; and (5) no indication for ACT according to the treating physician and/or multidisciplinary board. Patients who are pregnant, have had another malignancy in the previous 5 years, except for carcinoma in situ, or patients with contra-indications for fluoropyrimidines and/or oxaliplatin will be excluded.

Currently the Dutch guidelines recommend ACT for patients with pT4 tumors. However, there is large age- and hospital dependent variation in administration of ACT in this group and in clinical practice not all stage II patients with pT4 tumors will be offered ACT [27]. Therefore, we will include eligible patients with pT4 tumors without a recommendation for ACT according to their treating physician and use pT4 status as a stratification factor.

### Blood sample collection

Blood samples are collected before and 4–21 days after surgery for all patients included in the MEDOCC clinical study, predominantly comprising stage I, II and III CC patients (Table 1). Blood samples (two tubes of 10 ml per timepoint) are collected in Cell free DNA Streck Blood Collection Tubes for various research purposes, among which the MEDOCC-CrEATE trial.

**Table 1 Tab1:**
[figure not shown]
Standard Protocol Items for Intervention Trials (SPIRIT): schedule of enrollment, interventions and repeated measurements. ACT: adjuvant chemotherapy; ctDNA: circulating tumor DNA; QoL: quality of life. * Intervention group only. ** Intervention group only, if ctDNA is positive

### Randomization

About 1 week after surgery, when the histopathological report is finished, MEDOCC patients who are eligible for MEDOCC-CrEATE will be randomized 1:1 to the intervention or control arm using SLIM, an online platform to manage patient inclusion including a randomization service. The computer generated randomization schedule is stratified by T-stage and uses permuted blocks of random sizes. Allocation concealment will be ensured, as the service will not release the randomization code. Only patients randomized to the intervention arm will be informed about MEDOCC-CrEATE according to the TwiCs design [22].

### Experimental arm

After randomization, only patients randomized to the experimental arm will be asked separate informed consent for the immediate analysis of ctDNA status of the post-surgery sample. A small proportion of patients, estimated approximately 5–8% will have detectable ctDNA in their blood. These patients will be offered ACT. Patients decide whether they accept or refuse this treatment. Patients without detectable ctDNA will receive routine standard of care.

ACT will consist of 6 months of capecitabine and oxaliplatin (CAPOX) or 6 months of fluorouracil, leucovorin and oxaliplatin (FOLFOX). Treatment starts preferably within 8 weeks and not beyond 12 weeks after surgery.

During and after completing ACT routine follow-up will consist of regular visits at the surgical outpatient department, blood withdrawals for analysis of carcinoembryonic antigen (CEA) and imaging (standard ultrasound of the liver) according to current guidelines in the Netherlands. No additional imaging will be performed to prevent detection bias.

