### Control arm

In the control arm, patients will not be informed about the MEDOCC-CrEATE trial and receive routine follow-up care consisting of CEA tests every 3 months for the first 3 years and abdominal ultrasound or CT every 6 months in the first year and once a year afterwards. One year after surgery a colonoscopy is performed. Post-surgery blood samples will not be tested for ctDNA immediately, but will be analyzed batch-wise after several months without result disclosure to patients and their treating physicians.

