### Sample size considerations

The primary endpoint is the proportion of ctDNA positive patients starting with ACT. However, 2-year RR in the ctDNA positive patients after surgery is an important secondary endpoint and the power calculation is performed for this secondary endpoint. We estimate that, similar to effectiveness in stage III CC patients, ACT in ctDNA-based high-risk stage II CC patients will lead to a 30% absolute reduction of recurrences within 2 years after surgery. In the observational trial 79% of patients with detectable ctDNA experienced disease recurrence within 2 years after resection [21].

With a power of 80% and an alpha of 0.05, 30 patients with detectable ctDNA need to be included in both arms. Assuming a prevalence of ctDNA after surgery of 5%, and adjustment for loss to follow-up and rejection of adjuvant therapy in the intervention arm of 10%, a total sample size of 1320 patients is calculated (660 in each arm). We expect few patients with detectable ctDNA in the intervention group to refuse ACT, because patients are selected upfront for being in a physical condition to receive ACT and the established prognostic value of detectable ctDNA is high.

We assume that cross-over from the control arm to the intervention arm will not occur, because only eligible patients randomly selected in the cohort and allocated to the intervention arm will be informed about the trial and have the opportunity for immediate analysis of ctDNA. Patients in the control group will not be informed about the trial or their ctDNA status.

We assume that 90% of patients in the intervention arm with detectable ctDNA will be treated with ACT. The proportion of patients starting with chemotherapy, the primary endpoint, can in that instance be determined with a margin of error (width of the 95% confidence interval) of 11%.

We expect to complete recruitment of patients within 2–3 years with more than 20 participating Dutch hospitals.

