### Data analysis

Data will be analyzed according to the intention-to-treat principle for the primary endpoint and the secondary endpoint of 2-year RR in patients with detectable ctDNA after surgery. In this analysis we expect to compare 30 patients with detectable ctDNA who received ACT in the intervention arm with 30 patients with detectable ctDNA in the control arm, i.e. based on ctDNA analysis performed retrospectively, at least 3 months after surgery, and not disclosed to patients and treating physicians. The proportion of patients that experience a recurrence in both arms will be compared by means of a chi-square test. In addition, for other secondary endpoints and exploratory analyses we will analyze time-to-event outcomes in patients in both arms with detectable ctDNA after surgery. Differences in time-to-event outcomes will be analyzed by standard survival methods, e.g. Kaplan-Meier curves compared by log-rank tests. Cox’s proportional hazards models will be used for multivariable analysis.

Comparison of QoL of the ctDNA positive patients in both study arms will be done using repeated measurements methods and including ACT as factor. QoL will also be analyzed for the whole population in both arms of the study. Treatment differences at each QoL assessment time point will be compared by means of the Wilcoxon Rank Sum Test.

A lifetime horizon will be applied for the cost-effectiveness analysis, parametric survival functions will be used to extrapolate DFS and OS curves beyond 5 years.

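### ctDNA status depends on consent after randomisation in the experimental arm only, so the 2-year recurrence comparison is open to one-sided selection

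*Protocol article*

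**What the plan says.** Eligibility requires "informed consent for PLCRC and MEDOCC including consent for randomization in future trials and use of tissue", so a cohort-level consent precedes randomisation in both arms (Protocol article, Patient selection and recruitment). The arms then diverge:

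- **Experimental arm:** "only patients randomized to the experimental arm will be asked separate informed consent for the immediate analysis of ctDNA status of the post-surgery sample" (Experimental arm). The Fig. 1 caption says the same.
- **Control arm:** patients are not approached, since "Only patients randomized to the intervention arm will be informed about MEDOCC-CrEATE according to the TwiCs design" (Randomization). Their post-surgery samples "will be analyzed batch-wise after several months without result disclosure to patients and their treating physicians" (Control arm).

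On analysis: "Data will be analyzed according to the intention-to-treat principle for the primary endpoint and the secondary endpoint of 2-year RR" (Data analysis), the latter being confined to ctDNA-positive patients. The next sentence of that section expects 30 experimental ctDNA-positive patients who received ACT against 30 ctDNA-positive controls. It attaches retrospective testing to the controls only. The test is a chi-square on the proportion with recurrence.

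Sample size considerations takes 5% prevalence and adds 10% for loss to follow-up and refusal of adjuvant therapy, reaching 660 per arm. Test refusal is not named. The Experimental arm section puts the expected proportion of positives at about 5–8%.

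**The concern.** Consent after randomisation in one arm belongs to the trial-within-cohorts design. It does no harm to validity when decliners are analysed as randomised. Here the main recurrence comparison is confined to ctDNA-positive patients, and a patient enters that set only with a test result. An experimental patient who declines the immediate test has no described route into the set. The corresponding control, who would have declined if asked, is tested and stays in, and cannot be recognised. Limiting the experimental positives to those who received ACT adds a second filter on the same side.

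Post-surgery ctDNA status would define comparable subgroups if it were ascertained alike in both arms; as described, it is not. The stake is high because the article's closing paragraph ties clinical implementation to a difference in recurrence between the arms.

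**Working it through.** **1. The plan's own figures.** Inputs from Sample size considerations: control 2-year recurrence 79%, absolute reduction 30 points (so 49%), power 80%, alpha 0.05, prevalence 5%, allowance 10%.

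- Positives per arm: n = [z_α√(2p̄q̄) + z_β√(p₁q₁ + p₂q₂)]² / (p₁ − p₂)², with p̄ = 0.64. One-sided: [1.645 × 0.679 + 0.842 × 0.645]² / 0.09 ≈ 30.6, so 31, close to the stated 30. Two-sided it is 39. The article does not state sidedness. That is a separate matter, but the power figures below depend on it.
- Total: 30/0.05 = 600; 600 × 1.10 = 660 per arm; × 2 = 1320. Reproduced exactly.

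**2. Headcount if only consenters are tested.** Experimental positives = 660 × prevalence × (1 − d), where d is the test refusal rate. The article gives no value for d, so a range is assumed.

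| d (assumed) | Experimental positives at 5% | Control positives at 5% | Experimental positives at 8% |
|---|---|---|---|
| 0% | 33.0 | 33 | 52.8 |
| 10% | 29.7 | 33 | 47.5 |
| 20% | 26.4 | 33 | 42.2 |
| 30% | 23.1 | 33 | 37.0 |

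Break-even at 5%: 1 − 30/33 = 9.1%. Any loss to follow-up or ACT refusal draws on the same margin.

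**3. Selection under no treatment effect.** Suppose positive consenters have recurrence risk p and positive decliners p + g. All control positives then average p + d·g and tested experimental positives average p, so the spurious difference is d × g. For illustration only, with g assumed at 10–20 points: 0.10 × 10 = 1 point up to 0.30 × 20 = 6 points. If decliners do better, the sign reverses; if d or g is zero, the difference vanishes. The article supports no value of either.

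**4. Keeping decliners as randomised.** Assume decliners get no ACT and all positive consenters do. Experimental recurrence = 0.79 − 0.30(1 − d). Power = Φ{[(p₁ − p₂)√n − z_α√(2p̄q̄)] / √(p₁q₁ + p₂q₂)} with n = 33 per arm. For d = 10%, one-sided: (0.27 × 5.745 − 1.645 × 0.672)/0.645 ≈ 0.69, so power is 0.76.

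| d (assumed) | Experimental recurrence | One-sided power | Two-sided power | Positives per arm for 80%, one-sided |
|---|---|---|---|---|
| 0% | 49% | 0.83 | 0.73 | 31 |
| 10% | 52% | 0.76 | 0.64 | 38 |
| 20% | 55% | 0.67 | 0.55 | 47 |
| 30% | 58% | 0.58 | 0.45 | 60 |

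**The case against.** The strongest reply is that much of this is silence in a condensed article. Several stronger readings are tempting, and the article does not support them.

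- **Decliners never get a result.** A reader might infer this, but the separate consent is for immediate analysis. The earlier cohort consent may allow later batch testing, and no sentence excludes decliners. This stands as a limit on the point. Still, the article describes retrospective testing for controls alone.
- **The treated-patients wording is only loose.** The sentence states an expectation, and Secondary endpoints lists a separate per-protocol analysis of 2-year recurrence. That favours reading the main analysis as truly intention-to-treat, and is a reason to correct the sentence.
- **Sampling can follow allocation and so differ by arm.** Randomisation is "About 1 week after surgery, when the histopathological report is finished", while blood may be drawn up to day 21. But Blood sample collection sets one schedule for all MEDOCC patients, and the Discussion says all participants have post-surgery blood drawn. Nothing shows a difference between arms.
- **The primary endpoint overstates willingness.** With an assumed 20% test refusal and the planned 90% uptake, 0.8 × 0.9 = 72% of all experimental positives would start ACT. But the endpoint is defined as starting ACT after detection of ctDNA, so 72% answers a different question and does not correct the 90%.
- **The problem is already disclosed.** The Discussion says consent must be substantial for valid results, but supports this mainly by expected acceptance of ACT. That mitigates the point without resolving it.

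**Conclusion.** The point holds as a statement about how ctDNA status is ascertained and how the analysis set is described. As written, testing is conditional on consent after randomisation in one arm only, and the comparison labelled intention-to-treat is worded to take only treated positives from that arm. The 2-year recurrence comparison is therefore open to one-sided selection.

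It does not follow that the compared groups are certain to differ from the randomised ones. That depends on how many decline and whether they differ in prognosis, and the article gives neither. The 1–6 points above illustrate the mechanism and are not an estimate.

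The shortfall in numbers is conditional too. At the planned 5% prevalence, test refusal above about 9% leaves fewer than 30 experimental positives; at 8% it does not, even with 30% refusal. The primary endpoint stands as defined.

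**What to change.** 1. Test the stored post-surgery samples of experimental-arm test decliners in batches and undisclosed, as for controls, where the PLCRC/MEDOCC consent allows it and has not been withdrawn. The consent forms are not shown, so this must be checked against them.
2. Include all ctDNA-positive patients as randomised in the intention-to-treat analysis of 2-year recurrence.
3. In Data analysis, delete the restriction to patients who received ACT; it belongs with the per-protocol analysis.
4. Restate the power with an explicit allowance for test refusal, and state the sidedness used.
5. Optionally, report ACT uptake among all experimental-arm positives as a supplementary figure beside the primary endpoint.

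Randomisation need not be delayed until the sample is drawn to meet this point.

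**Cost.** Protocol wording and a few more assays, within the 660 per arm whose status the sample size already counts on; no new patient procedure. The real price is dilution: at assumed refusal of 10%, 20% and 30%, one-sided power with 33 positives per arm is about 0.76, 0.67 and 0.58 if decliners get no ACT. That loss follows from the plan's own intention-to-treat principle and should be stated openly.
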